## Abstract

**Background:**

Inflammatory bowel diseases (IBDs) are chronic inflammatory conditions of the gastrointestinal tract. Although adherence to IBD therapies is associated with improved clinical outcomes, overall adherence is poor. Consequently, there is a critical need to develop interventions that monitor adherence in real time and identify reasons for nonadherence to support clinical teams in initiating effective interventions. Recently, electronic- and web-based platforms have been developed to monitor adherence and guide interventions. A novel remote therapy monitoring (RTM) technology, the Tappt digital health system, has been developed to monitor real-time medication adherence patterns through smart label technologies, capture patient-reported outcomes and barriers to care, and process patient data through algorithms that trigger personalized digital and human touch points between clinical visits. Such a digital health solution enables care teams to proactively identify and mitigate nonadherence and worsening clinical outcomes.

**Objective:**

We propose a 12-month multicenter randomized controlled trial to assess the effectiveness of the Tappt digital health system on adherence, clinical outcomes, and health care use among patients diagnosed with IBD starting a new oral or subcutaneous therapy.

**Methods:**

The digital health system intervention will provide automatic measurement of medication adherence via smart labels for pill bottles or injectors as well as a monitoring platform for providers. The system will prompt patients to complete a two-item assessment of symptoms monthly using the PRO-2 scales for UC and Crohn disease, from which increased symptoms will be alerted to providers. Participants will be randomized 2:1 to the intervention group or the control group, which will receive standard of care. All participants are required to complete questionnaires at baseline as well as at 12, 26, and 52 weeks. Assuming an adherence rate of 0.65 and 0.9 among control and intervention participants, respectively, we will need to enroll 123 participants: 82 (66.7%) in the intervention group and 41 (33.3%) controls. We will compare adherence as measured by the medication possession ratio, defined as the number of days of supply of medication obtained during the observation period out of the total number of days in the observation period, in participants using the RTM versus those receiving standard of care. We will also compare clinical outcomes and health care use in participants using the RTM versus those receiving standard of care.

**Results:**

We anticipate starting recruitment in December 2022.

**Conclusions:**

Effective medication adherence monitoring and intervention programs need to be cost-efficient, pose little or no burden to the patient, record reliable data in real time, and provide actionable insights to the health care team. We anticipate the Tappt digital health system to improve the medication possession ratio, clinical outcomes, and health care use compared with standard of care.

**Trial Registration:**

ClinicalTrials.gov NCT05316584; https://clinicaltrials.gov/ct2/show/NCT05316584

**International Registered Report Identifier (IRRID):**

PRR1-10.2196/40382

## Introduction

### Background

Inflammatory bowel diseases (IBDs), comprising Crohn disease (CD) and ulcerative colitis (UC), are chronic, progressive, inflammatory conditions of the gastrointestinal tract that affect up to 3 million Americans [1]. IBD is thought to be driven by inappropriate immune responses to an altered gut microbiome, with a disease course characterized by remitting and relapsing episodes of inflammation, or flares.

Most patients with a chronic condition require long-term therapy. Evidence has demonstrated that suboptimal adherence is associated with poor clinical outcomes, including increased IBD activity and associated complications, worsened quality of life (QoL) [2], and higher health care use and costs [3]. In addition, nonadherence to biologic therapies may increase the risk for developing antidrug antibodies, leading to loss of response to therapy. Despite this, adherence to IBD therapies remains suboptimal. A recent survey administered to 322 patients with IBD found that 55% reported nonadherence, including forgetting or skipping medication owing to not feeling well [4]. Overall adherence to IBD medications ranges from 40% to 80%, depending on the patient population, medication class, data sources, and adherence quantification measures [5].

Adherence to oral IBD medications such as aminosalicylates and thiopurines ranges from 50% to 93% [6]. Studies evaluating adherence to biologic therapies are conflicting. Using a medication possession ratio (MPR)—calculated as the number of days of supply of medication obtained during the observation period out of the total number days in the observation period—of <100% as a definition of nonadherence in 365 patients with IBD treated with biologic therapies, adherence was highest for intravenous formulations (70%-83%) compared with subcutaneous biologics (47%-50%) [7]. Conversely, in a large multicenter prospective cohort study where adherence was defined as ≥80% using a visual analog scale, the majority of patients with CD and UC were considered adherent (88% and 86%, respectively) [8]. However, when comparing across medication classes, adherence was lowest for patients on rectal (68%) and oral (83%) therapies and highest for intramuscular (88%) and parenteral (87%) therapies [8]. Similar results were found in a recent study of 112 patients with IBD in the Manitoba cohort: 81% of the patients were considered adherent to their therapy using an MPR cutoff value of ≥90% [9].

The variance in adherence is in part due to inconsistent measurement. Objective and validated approaches include pill counts, refill counts, and pharmacological or biochemical markers; subjective approaches include validated measures, visual analog scales, and patient interviews. Some approaches may work better in certain settings, given that they measure adherence in different ways and at different time points [10]; for example, although validated measures are effective in clinical trials, they can be burdensome and time consuming in real-world practice. Furthermore, they do not capture day-to-day variability in adherence because the adherence measure summarizes medication-taking behaviors over a designated period [3]. Similarly, pharmacy records and insurance databases provide data that can be used to calculate MPR and percentage of days covered by the prescriptions, but they do not provide information on medication intake patterns and do not capture use of samples [10,11]. Patient interviews are the most efficient way to gather a complete picture of patient adherence, but they can be unreliable, given that patients tend to overestimate their adherence [10].

In recent years, electronic- and virtual-based platforms have been developed to monitor adherence routinely and guide appropriate interventions. These remote therapy monitoring (RTM) systems include electronic pill caps, electronic pill and needle boxes, bidirectional SMS text message reminders, and patient-facing mobile apps [10,12-14]. Although some of these have been successful at monitoring and improving adherence, they are limited by their battery requirement and cost as well as the survey fatigue of respondents. Furthermore, these solutions and apps collect data inconsistently and are not synchronized with clinical teams’ workflows in a real-time manner to identify patients at risk for nonadherence and drive actionable follow-up.

Synchronyx, which is based in Boca Raton, Florida, United States, has developed a scalable RTM and patient engagement solution called the Tappt digital health system. It consists of smart battery-free labels affixed to medication packages that transmit encrypted adherence data from the patient’s smartphone through a secure server; a patient-facing web application with access to personalized data and educational resources; and a centralized cloud-based and password-protected clinician portal that summarizes patients’ medication intake behaviors in real time at individual and aggregate levels, collects patients’ barriers to care and patient-reported outcomes (PROs), and triggers alerts to designated clinical teams.

### Preliminary Work

#### IBD Home Automated Telemanagement

For patients with IBD, we previously developed the IBD Home Automated Telemanagement (HAT) system, which consists of a laptop computer, an electronic weighing scale, and a physician web portal. The laptop computer and scale made up the patient home unit. The laptop computer administered questions on patient symptoms, adherence, and medication side effects and delivered educational messages, whereas the scale was used to regularly measure body weight [15,16].

We performed a 6-month open-label trial to assess the feasibility and patient acceptance of the IBD HAT system in patients with IBD. We predetermined that ≥80% adherence with self-testing would demonstrate feasibility. Patient acceptance of the HAT system was evaluated using the IBD HAT attitudinal survey. In total, 27 patients with IBD were recruited from the University of Maryland and Veterans Affairs Hospital in Baltimore, Maryland, United States. Participants continued to receive standard IBD care in addition to the weekly HAT sessions.

Of the 27 participants, 25 (93%) successfully completed the 6-month study. During the study, 89% (22/25) of the participants were adherent with weekly self-testing, and 91% (23/25) said that self-testing was not complicated. Of the 25 participants, 18 (73%) reported that they felt safer using the system, and 23 (91%) stated that they would agree to use the self-testing program in the future. Self-reported adherence with IBD medications was 90% throughout the study. Clinical disease activity, disease-specific QoL, and patient knowledge improved compared with baseline [17].

We then pursued a 12-month randomized clinical trial to assess the effectiveness of the UC HAT system compared with best available care (BAC). We modified the symptom diary and alert criteria to make them specific to UC and added action plans and electronic messaging for participants to communicate with the research team. Adults with UC from the University of Maryland and Veterans Affairs Hospital in Baltimore were randomized to self-testing with the UC HAT system weekly or BAC. All participants underwent visits at baseline and every 4 months. Disease activity was measured using the Seo index [18,19], disease-specific QoL was measured using the Inflammatory Bowel Disease Questionnaire [20], and medication adherence was measured using a medication adherence scale [21]. We randomized 47 patients, and 29 (62%) completed the study. After adjustment for baseline QoL scores, participants in the UC HAT arm had a strong trend toward decreased Seo index scores from baseline (mean –11.9, SD 6.6; *P*=.08). Furthermore, after adjustment for baseline disease knowledge, participants in the UC HAT arm had a significant increase in QoL scores from baseline (mean 12.5, SD 5.9; *P*=.04), whereas participants in the BAC arm had nonsignificant decreases in QoL scores from baseline (mean –3.8, SD 5.3; *P*=.47). The difference in change in QoL scores from baseline between the UC HAT and BAC arms at 12 months was significant. Self-reported adherence to medical therapy was low in both groups at baseline (BAC: 45% and UC HAT: 40%). Adherence rates increased in both groups but were not significantly different at any time point after baseline. Both arms had poor IBD knowledge at baseline, with improvement at the 12-month follow-up; however, there was not a significant difference between the UC HAT and BAC arms at the 12-month follow-up [22]. Our results suggested that the randomization process was inadequate because participants in the UC HAT arm had higher rates of immune suppression use and greater impairments in QoL than participants in the BAC arm. We suspect that the baseline differences in favor of the BAC arm impaired our ability to demonstrate a treatment effect of the UC HAT system. This hypothesis is supported by the findings of clinically important improvements in disease activity and QoL from the baseline to the 12-month visit in the UC HAT arm. Furthermore, after adjustment for baseline disease knowledge, a significant improvement in QoL was noted in the UC HAT participants.

#### Telemedicine for Patients With IBD

We then conducted a multicenter randomized controlled trial to assess the effectiveness of telemedicine for patients with IBD (TELE-IBD) weekly (TELE-IBD W) or every other week (TELE-IBD EOW) compared with BAC. Patients completed self-assessments via SMS text messages, assessment of weight was completed through use of an electronic scale and manually entered by the participant, and educational messages were sent either weekly or twice weekly throughout the trial. We recruited 348 participants (n=116, 33.3%, TELE-IBD W; n=115, 33%, TELE-IBD EOW; and n=117, 33.6%, BAC controls), including 236 (67.8%) participants with CD and 112 (32.2%) with UC or indeterminate colitis. Of the 348 participants, 259 (74.4%) completed the final 12-month visit. Clinical indices of CD activity using the Harvey-Bradshaw Index (HBI) decreased in the control, TELE-IBD EOW, and TELE-IBD W groups (*P*=.16). The decreases in HBI scores over time were significant in all groups (*P*<.001) but not different among the groups (*P*=.18). Clinical indices of UC activity using the Simple Clinical Colitis Activity Index (SCCAI) decreased in the control, TELE-IBD EOW, and TELE-IBD W groups (*P*=.41), but they were significant only in the controls (*P*=.01) and not different among the groups (*P*=.25). IBD QoL scores increased in the control, TELE-IBD EOW, and TELE-IBD W groups (*P*=.42) but were significant only in the TELE-IBD EOW group (*P*=.03) and not different among the groups (*P*=.95). However, use of health care resources was different among the groups, with participants in the TELE-IBD arms experiencing lower total and IBD-related hospitalization rates and higher number of noninvasive diagnostic tests, telephone calls, and electronic messages [23]. In addition, those in the TELE-IBD arms had a greater improvement in Crohn’s and Colitis Knowledge scores [24] than those in the standard of care group. General self-efficacy scores improved in all arms during the trial but were not different among the groups [25,26]. In an analysis of intervention participants only, adherence increased with depressive symptoms in those who were aged ≤40 years (*P*=.02), but there was no association between depressive symptoms and adherence in those who were aged >40 years (*P*=.53) [27]. A follow-up qualitative study demonstrated that participants identified clear benefits of the TELE-IBD system, including a better understanding of the disease process, monitoring of symptoms, and feeling of connection to the health care team. Both adherent and nonadherent participants preferred a flexible system that was personalized, included targeted education, and promoted self-management [28].

### Aims

On the basis of the aforementioned preliminary work demonstrating that technology has the capacity to improve medication adherence and clinical outcomes, there is a critical need to integrate interventions that are affordable and practical to monitor adherence in real time. In addition, interventions that aim to identify reasons for nonadherence, intentional or unintentional, should be prioritized to support clinical teams in tailoring adherence interventions to each unique patient [10,29]. As such, we propose a 12-month multicenter randomized controlled trial to assess the effectiveness of an RTM solution, the Tappt digital health system, on adherence, clinical outcomes, and health care use among patients with IBD starting a new oral or subcutaneous therapy. Specifically, we will (aim 1) compare adherence as measured by the MPR in participants using the digital health system versus those receiving standard of care and (aim 2) compare clinical outcomes and health care use in participants using the digital health system versus those receiving standard of care.

## Methods

### Overview and Population

The proposed study is a multicenter randomized controlled trial to be conducted over 12 months. Participants in the intervention arm will be encouraged to verify medication adherence using the Tappt digital health system. This system will provide automatic measurement of medication adherence via smart labels for pill bottles or injectors as well as a monitoring platform for providers. In addition, the Tappt system will prompt patients to complete an assessment of symptoms monthly using the PRO scale, 2-item version (PRO-2) for UC and CD; if symptoms worsen, alerts will be triggered to providers. Participants randomized to the control group will receive standard of care. All participants are required to complete questionnaires at baseline and at 12, 26, and 52 weeks.

### Study Schedule

All participants are required to complete electronic data entry forms at baseline and at 12, 26, and 52 weeks. Adherence, disease activity, QoL, PROs, IBD self-efficacy, and health care use will be measured at each time point during the 1-year study (Table 1). Demographic and clinical information will be collected at the baseline visit.

**Table 1 table1:** Schedule of events for the study.

Instrument	Category	Source	Baseline	Week 12	Week 26	Week 52
Demographics	Demographics	Patient	✓			
Clinical history	Clinical information	Provider or site	✓			
Medication adherence	Adherence	Patient		✓	✓	✓
MARS-5^a^	Adherence	Patient	✓	✓	✓	✓
Health care use	Health care use	Patient	✓	✓	✓	✓
Modified Harvey-Bradshaw Index	Disease activity: CD^b^	Patient	✓	✓	✓	✓
Simple Clinical Colitis Activity Index	Disease activity: UC^c^	Patient	✓	✓	✓	✓
C-reactive protein	Disease activity	Provider or site	✓	✓	✓	✓
Calprotectin	Disease activity	Provider or site	✓	✓	✓	✓
Simple endoscopic score: CD	Disease activity	Provider or site	✓	✓	✓	✓
Mayo Endoscopic Score	Disease activity	Provider or site	✓	✓	✓	✓
PROMIS^d^ Global Health Scale	Quality of life	Patient	✓	✓	✓	✓
PROMIS anxiety	Mental health	Patient	✓	✓	✓	✓
PROMIS depression	Mental health	Patient	✓	✓	✓	✓
PROMIS sleep disturbance	Mental health	Patient	✓	✓	✓	✓
PROMIS fatigue	Disease activity	Patient	✓	✓	✓	✓
PROMIS pain interference	Disease activity	Patient	✓	✓	✓	✓
PROMIS physical function	Frailty	Patient	✓	✓	✓	✓
IBD^e^ self-efficacy	Self-efficacy	Patient	✓	✓	✓	✓

^a^MARS-5: Medication Adherence Report Scale-5.

^b^CD: Crohn disease.

^c^UC: ulcerative colitis.

^d^PROMIS: Patient-Reported Outcome Measurement Information System.

^e^IBD: inflammatory bowel disease.

### Study Population

Patients will be recruited for this study from 5 clinical centers at the University of Maryland School of Medicine, University of Cincinnati School of Medicine, NYU Grossman School of Medicine, University of North Carolina School of Medicine, and Vanderbilt University School of Medicine.

Inclusion criteria will include (1) aged ≥18 years; (2) documented IBD based on usual diagnostic criteria, including clinical symptoms and findings from endoscopy, radiology studies, and histology [30]; (3) initiation of treatment with a new oral or subcutaneous treatment for IBD; (4) access to a smartphone with a reliable data plan or Wi-Fi access; and (5) ability to understand the protocol and provide informed consent in English. Exclusion criteria will include (1) inability to speak and read English or comply with the study protocol; (2) the presence of an ileostomy, colostomy, ileoanal pouch anastomosis, or ileorectal anastomosis; (3) initiation of oral corticosteroids only without concurrent use of an oral or subcutaneous maintenance therapy; (4) imminent surgery within the next 60 days; (5) history of short bowel syndrome; or (6) uncontrolled medical or psychiatric disease.

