### Study Conduct

Eligible patients will be approached by research staff at the time of routine clinical visits or via telephone and provide informed consent. All of the participants’ concomitant medications will be continued during the study. Corticosteroids will be tapered at the discretion of the investigator. Addition of new IBD medications will be allowed during the study. If the new medication is an eligible oral or subcutaneous addition to existing therapy, this will be tracked using the approach that was used to track the original medication during the initial treatment. If the new medication replaces the initial therapy, the replacement medication will be similarly tracked.

Participants will be randomized 2:1 to receive either remote monitoring or standard of care using a random permuted block design with randomly varied block sizes. Participants will be stratified based on study site and disease subtype (CD vs UC or indeterminate colitis). We chose to stratify on these variables because they could affect the response to the intervention; stratification will ensure balance of these covariates among the study groups. The randomization order will be computer generated, and group assignment will be made when a new participant is enrolled into the study by the clinical site. The site investigators and research staff will remain blinded to the randomization order. The participants and physicians will not be blinded to the group assignment; however, we will attempt to minimize measurement bias by collecting outcome data through electronic data capture directly from participants.

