### Intervention Group

Eligible patients will complete a baseline survey gathering demographic and clinical information. Upon enrollment, the intervention participants will activate their account to access the patient-facing Tappt web application, which includes the individual participants’ medication regimen information, upcoming doses, and adherence data. The web application also includes a curated resource library with links to educational material on the Crohn’s and Colitis Foundation website, expert-led video modules on each IBD medication class, and training videos on how to use the system and seek support. The web application also allows patients to respond to surveys related to nonadherence or PROs. The system uses algorithms to send participants personalized alerts and reminders for medication doses or survey completion through SMS text messages.

After providing training to the intervention participants on how to use the Tappt system, the research team will input into the system the intervention participants’ deidentified information as well as the medication to be tracked, dose, and frequency of dosing. The research team will then assign smart labels to the participants’ medication regimen, which will be used by the participants to record their medication use. The research team will also walk each study participant through the Tappt system and explain how to label and scan medication and how to complete all required surveys. Along with the first medication, the corresponding smart labels to be affixed to the pill bottle, pen, or syringe container of the newly prescribed medication will be shipped to the participants. Participants will receive sufficient labels for dosing of 90 days of the medication to be tracked, plus an additional 2 to 6 labels to account for lost or damaged labels and dose escalation. Participants will receive enough labels until their next assessment (ie, a participant on mesalamine 2.4 g daily will receive 90 labels). Changes in dose of medications for the intervention participants will be monitored on a weekly basis by study coordinators. Any change in dosing will be updated on the Tappt clinician portal; labels will be reassigned to the new dosing frequency, and a new set of smart labels will be sent to the participants for the next 90-day dosing period.

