### Outcomes and Outcome Measures

#### Overview

The outcome measures outlined in the following sections will be assessed at baseline and at 12, 26, and 52 weeks after initiating treatment. All outcome measures will be captured electronically and will not require a study or office visit.

The primary outcome of the proposed study will be the difference in mean MPR between the intervention and control groups during the 12-month study. The mean MPR will be calculated as follows:

MPR = number of days’ supply of medication obtained during observation period / total number of days in observation period.

If a participant discontinues therapy but initiates treatment with another eligible medication, the MPR will continue to be calculated. Any delay in initiating new treatment will be adjusted for the total number of days in the observation period (ie, if drug A is discontinued and drug B is started 2 weeks later, the observation period will be 365 – 14 = 351 days); for example, if a participant is prescribed oral mesalamine (1.2 g), 4 tablets daily, for 90 days (dispense 360) with 2 refills between months 6 and 12, the MPR would be 100%. Likewise, if a participant is prescribed ustekinumab 90 mg subcutaneous every 8 weeks (dispense 1 syringe) with 2 refills between months 6 and 12, the MPR would be 66%. Data on medication use will be self-reported by participants at each time point. However, we will randomly validate participant report via chart review of pharmacy data for 20% of the participants. Participants will report the date the medications of interest were filled as well as the number of days’ supply of medications filled. Self-reported adherence will be assessed with the Medication Adherence Report Scale-5 questionnaire (Table 2). Scores for each item are summed to give a total score, with higher scores indicating higher levels of reported adherence [33].

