The secondary outcome of the proposed study will be the difference in health care use between the intervention and control groups during the 12-month study. For health care use, we will use a composite end point, including counts of hospitalizations, urgent care or emergency room visits, IBD-related surgeries, telephone calls (primary care and IBD provider), endoscopic procedures, imaging examinations, and blood and stool testing. We will also assess new prescriptions for corticosteroids (prednisone and budesonide) at each time point during the study period. The total events will be adjusted per 100 patient years of follow-up because the 2 groups will be unequal in number. In addition, we will evaluate each outcome individually. The relatedness of hospitalization and urgent care or emergency room visits to IBD will be determined as well. Information will be obtained from patient self-report at each assessment. This approach has been validated in patients with IBD using a modification of the Canadian Community Health Survey [34]. However, we will validate participant self-report via chart review for 20% of the participants, randomly selected.

**Table 2 table2:** Medication Adherence Report Scale-5 questionnaire.

Item	Scoring				
	Always	Often	Sometimes	Rarely	Never
I forget to take my medication	1	2	3	4	5
I alter my medication dose	1	2	3	4	5
I stop taking my medication for a while	1	2	3	4	5
I decide to miss out a dose of my medication	1	2	3	4	5
I take less medication than instructed	1	2	3	4	5

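### Exclusion 3 asks only for concurrent use of maintenance therapy, so a patient whose sole new drug is an oral corticosteroid can qualify, and the tracked drug for the 12-month MPR is then unsettled

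*Protocol article*

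**What the plan says.** All references are to the protocol article.

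- **Study Population, inclusion 3** requires "initiation of treatment with a new oral or subcutaneous treatment for IBD". The word maintenance does not appear.
- **Study Population, exclusion 3** removes "initiation of oral corticosteroids only without concurrent use of an oral or subcutaneous maintenance therapy". The maintenance therapy has to be in use; nothing says it has to be new.
- **Aims** describe the population as patients with IBD who are starting a new oral or subcutaneous therapy.
- **Intervention Group** has "smart labels to be affixed to the pill bottle, pen, or syringe container of the newly prescribed medication" shipped to participants.
- **Study Conduct** says "Corticosteroids will be tapered at the discretion of the investigator". For drugs added later it says "If the new medication is an eligible oral or subcutaneous addition to existing therapy, this will be tracked", without defining which additions are eligible.
- **Outcomes and Outcome Measures, Overview** makes the primary outcome the "difference in mean MPR between the intervention and control groups during the 12-month study". Its one rule on stopping is "If a participant discontinues therapy but initiates treatment with another eligible medication, the MPR will continue to be calculated", with the untreated gap between the two drugs taken out of the denominator (365 − 14 = 351 days in its example).
- **The same Overview** lists steroid prescribing among the outcomes: "We will also assess new prescriptions for corticosteroids (prednisone and budesonide) at each time point during the study period".

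**The concern.** Exclusion 3 shows that the authors foresaw patients who start only a steroid and wanted to keep them out. It also shows that a new oral steroid would otherwise satisfy inclusion 3, since the exclusion would have nothing to do if it did not. But it closes the door only on patients with no maintenance therapy. A patient who has taken the same mesalamine or subcutaneous biologic for years, flares and starts prednisone meets inclusion 3 through the steroid and escapes exclusion 3 through the old drug.

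Once that patient is enrolled, the plan does not settle which drug the MPR describes. If it is the steroid, a 12-month possession ratio is being calculated for a drug that is meant to end, and the ratio reflects the length of the course more than the patient's behaviour. If it is the old maintenance drug, the ratio can be calculated, but the participant lies outside the new-starter population that the trial sets out to study. Five sites could settle this in different ways.

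**Working it through.** **Step 1. Apply the criteria to one patient.** Take a patient on established oral or subcutaneous maintenance whose only new drug is an oral corticosteroid.

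| Provision | Test | Result |
|---|---|---|
| Inclusion 3 | New oral or subcutaneous IBD treatment? | Yes, the steroid |
| Exclusion 3 | Steroid only, with no maintenance in use? | No, maintenance is in use |
| Aims | Starting a new therapy? | Only if the steroid counts as that therapy |
| Intervention Group | Which drug is newly prescribed? | The steroid |
| Study Conduct | Is that drug meant to continue for 12 months? | No, it is tapered |

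The first two rows admit the patient. The other three do not fit together for that patient.

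**Step 2. What the MPR would be if the steroid were tracked.** The formula is MPR = days' supply obtained / days in the observation period. The documents give no course length, so the lengths below are assumptions, each taken in full, over a denominator left at 365 days:

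- 6 weeks: 42/365 = 0.12
- 8 weeks: 56/365 = 0.15
- 12 weeks: 84/365 = 0.23
- 16 weeks: 112/365 = 0.31

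The 365-day denominator is also an assumption. The Overview adjusts it only when another drug follows. If the period were instead closed at the end of the course, the 8-week patient would score 56/56 = 100%. The same behaviour scores 15% or 100% according to a rule that is not stated.

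**Step 3. Reproduce the plan's sample size, then show the direction of the effect.** Statistical Analyses gives adherence rates of 0.65 and 0.90, allocation 2:1, type I error 0.05 and power 0.9. With the pooled two-proportion formula, two-sided and without continuity correction:

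- Pooled rate p̄ = (0.65 + 2 × 0.90)/3 = 0.8167
- Controls n = [1.96 √(1.5 × 0.8167 × 0.1833) + 1.2816 √(0.65 × 0.35 + 0.90 × 0.10/2)]² / 0.25² = (0.929 + 0.669)² / 0.0625 = 40.9, so 41
- Total = 41 + 82 = 123, as stated; power at 41/82 is 0.901

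The eligibility wording does not alter this figure. To see which way it pushes, suppose a share f of each arm were steroid-only entrants, all classed as non-adherent because their course ended. The rates become 0.65(1 − f) and 0.90(1 − f), and

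power = Φ{[d√41 − 1.96 √(1.5 p̄(1 − p̄))] / √(p₁(1 − p₁) + p₂(1 − p₂)/2)}, where d = p₂ − p₁.

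| Assumed f | Rates | Difference | Power at 41/82 |
|---|---|---|---|
| 0 | 0.650 v 0.900 | 0.250 | 0.90 |
| 5% | 0.6175 v 0.855 | 0.2375 | 0.83 |
| 10% | 0.585 v 0.810 | 0.225 | 0.75 |
| 20% | 0.520 v 0.720 | 0.200 | 0.59 |

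For f = 10%: (0.225 × 6.403 − 1.059)/0.565 = 0.674, and Φ(0.674) = 0.75. No value of f can be taken from the documents, so the table shows direction and sensitivity; it is not an estimate. It also stays on the scale of adherent proportions that the sample size uses, whereas the planned test compares mean MPRs.

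**The case against.** The strongest reply is that the article never names a steroid as a tracked drug and that its context points the other way. The worked examples are mesalamine and ustekinumab. Study Conduct mentions steroid tapering straight after saying that concomitant medications continue. The Overview and the section on disease activity record new steroid use as an outcome. The label instruction governs what intervention participants scan, while the MPR in both arms comes from reported fills of drugs of interest. A sensible site might therefore never label a steroid. This stands, and it rules out saying that the steroid becomes the drug behind the primary outcome. A reader might infer that from the label instruction, but the text does not say it.

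A reader might also infer that steroid courses added during follow-up are tracked, so that one prescription counts both towards adherence and as an outcome. That is not supported either. Exclusion 3 decides who enters, not which additions are tracked, and an undefined eligible addition has not been shown to include steroids.

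It can further be said that a drug list belongs in the full protocol or a manual. That is fair, and the missing list is not the point here. The two eligibility criteria are stated in full, and they are what admits the patient.

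Finally, how often this would happen is unknown. With the same share in each arm, as assumed above, the effect would be dilution and not bias between arms. Both points stand and limit the weight of the finding.

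**Conclusion.** The point holds in a limited form. As written, inclusion 3 and exclusion 3 together admit a patient on established maintenance whose only new drug is an oral corticosteroid. Following the remaining text leads either to a tapered drug as the index drug or to a participant who is not starting a new therapy. Both conflict with the Aims, and the first also conflicts with a 12-month MPR.

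The size cannot be estimated. The 15% score rests on three conditions: the steroid is tracked, the course lasts an assumed 8 weeks, and the denominator stays at 365 days. The loss of power rests on assumed shares and on classing every such entrant as non-adherent. What is certain is the wording; what is conditional is its effect on the primary outcome. The point merits correction because the change is cheap and protects that outcome. It does not put the validity of the trial in doubt.

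**What to change.** 1. **Inclusion 3:** make the qualifying event the start of a new oral or subcutaneous *maintenance* therapy for IBD.
2. **Exclusion 3:** state that a patient whose only newly started drug is a corticosteroid does not qualify, *whether or not maintenance therapy is already in use*. A patient who starts a steroid together with a new maintenance drug would remain eligible.
3. **Study Conduct, Intervention Group and the outcomes Overview:** reconcile these with one sentence saying that corticosteroids are not the tracked drug, enter neither numerator nor denominator of the MPR, and are counted only under the steroid outcome.

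These changes concern eligibility and the definition of the endpoint. They leave steroid use and tapering as the protocol has them. The cost is two eligibility lines, one sentence and a slightly smaller eligible pool. The article describes recruitment as still to start, so the change could be made before anyone is enrolled.
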